## Abstract

**Background:**

Telehealth use during family-centered rounds in the neonatal intensive care unit has been shown to shorten length of hospitalization and improve breastfeeding outcomes. For families who speak languages other than English, access to and use of telehealth technologies can be impeded by lack of interpreter services. We aim to evaluate the feasibility of telehealth use during family-centered rounds in the neonatal intensive care unit for families who speak languages other than English.

**Methods:**

In this study proposal, we will conduct an intervention evaluation using the RE-AIM (Reach, Effectiveness, Adoption, Implementation, Maintenance) framework to assess the feasibility of telehealth use during family-centered rounds among families who speak languages other than English in a single-arm feasibility trial. We will provide language-appropriate materials to assist parents with accessing the telehealth technology and bring interpreters into the telehealth encounter directly with neonatal providers. All eligible infants whose families speak languages other than English in a single-site level 4 neonatal intensive care unit during the study period will be included. These families can participate in hospital rounds via telehealth, in-person, or not participate in hospital rounds. We will examine feasibility objectives that assess parental uptake of telehealth for rounds, parental participation in rounds, presence of a certified medical interpreter, telehealth technical issues, and parental survey response rates. We will conduct a mixed methods implementation evaluation using the RE-AIM framework. Exploratory outcomes include parent attendance, length of hospitalization of the infant, human milk feeding, frequency of medical error, parent-reported experience, parental comfort with their child’s care, and parental quality of life will be collected.

**Discussion:**

This study will aid in understanding gaps to telehealth care in languages other than English. We believe this approach will improve health outcomes for hospitalized premature infants, understanding of medical conditions, improve parental quality of life, and reduce inequities in access to healthcare via telehealth technologies.

**Trial registration:**

NCT05917899 Limited English Proficiency Virtual Family-Centered Rounds, first posted June 26, 2023, last update posted November 11, 2024.

## Introduction

Family-centered rounds (FCR) is an essential component of successful pediatric inpatient care that incorporates rounding with the entire clinical team including the parents or guardians (“parents” hereafter) of hospitalized children [1]. For parents, FCR has been shown to reduce anxiety and improve understanding of their child’s medical condition [2, 3]. FCR is associated with improved patient outcomes, reduced exposure to hospital errors, and a shortened length of stay [2]. For critically ill hospitalized infants in the neonatal intensive care unit (NICU), FCR improves parental understanding of the medical conditions of their child and increases shared decision making [4]. Other research has demonstrated that FCR in the NICU is associated with a reduced length of stay and improved breastfeeding outcome [5].

Parental participation in bedside FCR in the NICU can be impeded by limited access to the hospital. NICU care in the United States is increasingly regionalized in large medical centers and many families, especially those living in rural areas, live far from the hospital. Parents can have difficulty attending in person rounds as they may need to return home to care for other children or return to work [6]. Communication and FCR participation for families with language preference other than English (LOE) can be hampered by the need for translation services [7]. Hospitalized children of parents with LOE are more likely to experience adverse events and have worse healthcare outcomes than children of parents with English proficiency [8, 9]. Our group previously demonstrated that the use of videoconferencing with English-speaking families improves engagement in FCR (herein vFCR) and allows families to participate in FCR from home [5].

Despite these promising results, vFCR has potential limitations that require further investigation and resolution. Before broad implementation of vFCR, careful study is needed to prevent the widening of disparities based on language preference and other social factors. Previous work has demonstrated large disparities in access and use of videoconferencing technology within healthcare settings by patient age, gender, race and ethnicity, insurance, and language, whereby families with LOE are half as less likely to have access to pediatric telemedicine care as English-speaking families [10].

### Objectives and trial design

Families with LOE should be prioritized when designing pediatric hospital-based research and implementing evidence-based clinical guidelines. Research in what influences the reach, adoption, and impact of telehealth among diverse groups is critically needed [11, 12]. The Reach, Effectiveness, Adoption, Implementation, Maintenance (RE-AIM) framework is a widely adopted implementation science framework that explicitly focuses on these design and implementation processes [13]. We will use the RE-AIM framework—with the RE-AIM extension to promote sustainability and health equity [14]—to conduct an intervention evaluation that explores the dynamic contextual factors influencing the vFCR intervention implementation for LOE families. In the quantitative phase, we will test the feasibility of vFCR among LOE parents of hospitalized infants in the NICU in a single-arm feasibility trial by providing language-appropriate materials to assist with accessing the vFCR technology and bringing interpreters into the vFCR encounter. In the qualitative phase, we will conduct qualitative interviews with NICU staff and LOE participants about the use of vFCR in the NICU. We will apply the RE-AIM framework [13, 15] to conduct an implementation evaluation within this trial. We will incorporate the RE-AIM extension, which is designed to promote sustainability and health equity [14], by exploring intervention evolvability (adaptability to long-term, dynamic contexts) and by considering equity across all RE-AIM dimensions. We will use a mixed methods approach with a convergent design to merge and categorize the data using the RE-AIM framework [16]. Our research group has reported previously that vFCR is technologically feasible, does not burden the NICU team, and parent-reported outcomes can be collected [5]. As this technology has already been implemented in the study site NICU, the objective of this study is to optimize FCR for LOE families and improve outcomes of hospitalized infants and their families.

## Methods

Reporting of this trial protocol follows the SPIRIT guideline for reporting trial protocols [17]. This study has been registered at clinicaltrials.gov (NCT05917899).

### Setting and population

This study will take place in a 121-bed children’s hospital within a large academic medical center in Northern California, USA. This hospital NICU has 49 beds and accepts patients from over 33 counties from a 65,000-mile region that includes Northern California, Southern Oregon, and Nevada.

Family units will be included in this trial and are defined as the hospitalized infant(s) and their parent(s) or guardian(s). Eligible families will have an infant who is < 365 days of age admitted to the NICU and at least one adult (aged 18 years or older) parent with a preferred language that is other than English. Exclusion criteria are families with restrictions placed by child protective services (such as restricted access to patient information or limited visitation), families previously enrolled in this trial on a prior NICU admission, and/or families already enrolled in a different trial that includes a FCR intervention.

### Study overview

This single-arm feasibility trial will assess the use of vFCR for LOE families with hospitalized infants in the NICU. Over a 12-month study period, we will conduct the quantitative phase and enroll all eligible family units, allowing accurate measurement of denominator values for feasibility objectives. Beginning in the first year and continuing into the second year of the study, we will conduct the qualitative phase and mixed methods evaluation.

We will invite the parents of enrolled family units to subscribe to use vFCR, by providing their contact information (i.e., cell phone number or email) to receive a secure link to join vFCR each weekday morning, excluding university holidays. In this way, subscribed parents have the option to participate in rounds via vFCR with video medical interpreting services or through usual care. Usual care is defined as attending FCR at bedside with a medical interpreter available or no participation in rounds. If family units have more than one parent listed in the electronic health record (EHR), both parents will be separately invited to subscribe to vFCR.

### Participant outreach

A research coordinator will make three attempts to contact each eligible parent until they decline or accept the invitation to subscribe to vFCR. Subsequently, every 2 weeks, new invitations will be sent to those who initially declined participation in vFCR. We will repeat outreach every 14 days because we learned in our previous NICU vFCR pilot trial that sometimes parents decline and then change their decision and would appreciate continued outreach to subscribe to use vFCR throughout their child’s hospitalization [5].

### Intervention

During daily rounds, a computer mounted on a medical grade pole with wheels and an omnidirectional microphone, a speaker, and a video camera will be taken on rounds to conduct the telehealth visits during vFCR. Our study site utilizes Health Insurance Portability and Accountability Act (HIPAA) compliant software called ExtendedCare for telehealth visits; this software launches directly from the patients’ chart in the EHR and integrates with the video medical interpreting platform, Martii. During rounds, the NICU team will launch the application and send a link to the vFCR through ExtendedCare by the participant’s preferred mode of communication (text or email). The link connects the parent directly to vFCR and does not require an additional download or application to use. A video interpreter will be invited to the vFCR when the parent is present. FCR rounds will then proceed with the NICU team. Parents of enrolled participants are not required to participate in vFCR and can join vFCR as frequently as they desire, come to the bedside for in-person FCR, or not participate in rounds at all. If there are technical difficulties, a help desk is available 24 hours per day, 7 days per week for the ExtendedCare application.

### Outcomes

Trial protocol outcome measures are viewable in Table 1.

**Table 1 Tab1:** vFCR study outcomes

Outcome name	Outcome type	Data source
LOE Parent subscription	Primary feasibility objective	Research team logs, EHR
vFCR use	Feasibility objective	Observation of rounds, Extended Care usage report
Interpreter use during vFCR	Fidelity objective	Observation of rounds, Extended Care usage report for LOE
Technical issues during vFCR	Feasibility objective	Observation of FCR, parent report, helpdesk technical issues log
Data collection	Feasibility objective	Parent surveys
Parent FCR attendance	Exploratory	Observation of rounds
Parent experience	Exploratory	Child HCAHPS survey
Parent activation	Exploratory	P-PAM survey
Parent quality of life	Exploratory	PedsQL Family Impact Module survey
Length of stay, days	Exploratory	EHR
Breast milk feeding	Exploratory	EHR
Adverse events / errors	Exploratory	EHR and solicited reports

*FCR* family-centered rounds, *EHR* electronic health record, *LOE* language preferred other than English, *vFCR* videoconferencing family-centered rounds, *HCAHPS* Child Hospital Consumer Assessment of Healthcare Providers and Systems survey, *P-PAM* Parent-Patient Activation Measure, *PedsQL Family Impact Module* measures parental quality of life and family functioning

### Feasibility objective outcomes

We will test the feasibility of conducting a trial for vFCR in NICU patients with LOE parents. Feasibility will be assessed through the following objectives (Table 2):Objective 1 (primary feasibility objective) will measure the reach of vFCR for LOE families and will be met if at least 75% of enrolled families have at least one parent who subscribes to use vFCR.Objective 2 will monitor uptake of vFCR and will be met if at least 70% of enrolled families use vFCR at least once during their infant’s hospitalization. We will measure the percent of enrolled families that participate in vFCR by tracking logins to the ExtendedCare application that is used for parent-to-provider video access during vFCR.Objective 3 will measure the fidelity the intervention and will be met if at least 95% of vFCR with a parent in attendance whose language preference is other than English includes a professional medical interpreter in the parent’s preferred language.Objective 4 will measure the technical feasibility and will be met if at least 90% of vFCR encounters have no technical issues. This will be assessed using vFCR observations, parent solicited reports, and reviewing the hospital helpdesk technical issues log during the study period.Objective 5 will assess the feasibility of survey data collection with a goal of survey response rates being at least 75% and with missingness for each variable of interest being less than 10%.

**Table 2 Tab2:** Feasibility objectives

Objectives	Indicator	Criteria for success
*Feasibility* of reach of vFCR	At least one LOE parent subscribes to vFCR	Subscription of at least one parent to vFCR will be at least 75% among LOE-enrolled families
*Feasibility* of uptake of vFCR	Use of vFCR during the trial period	Parent use of vFCR at least once will occur among at least 70% of enrolled families
*Feasibility* of intervention fidelity	Interpreter use for vFCR encounters with a parent in attendance with LOE	Use of a professional interpreter will occur in at least 95% of vFCR encounters that have a LOE parent in attendance
*Feasibility* of technology	Technical issues	Among attempted vFCR encounters, at least 90% will have no technical issues
*Feasibility* of data collection	Survey response for survey-derived outcome	Survey response rate will be at least 75%; all data elements will have less than 10% missing values

*vFCR* virtual family-centered rounds, *LOE* language preferred other than English

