Exploratory outcomes of parent experience, parental activation, and parent quality of life will be measured at hospitalization discharge through a survey packet. Surveys will be administered to one parent per enrolled family; this parent will be the parent with a language preference other than English. For families with more than one parent with a language preference other than English, the family will select which parent will complete the survey packet. Survey packets will be translated into the six most spoken languages among parents of infants in our NICU (Spanish, Russian, Pashto, Arabic, Farsi, Punjabi). For parents with a preferred language other than these six languages for whom we will not have prepared language-appropriate packets, we will administer the surveys verbally using a professional interpreter. Surveys will be distributed at the time of NICU discharge. Non-respondents will be followed up 7 days after discharge. If surveys are not returned by 21 days post discharge, the survey will be considered a non-response.

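### The primary objective has two numerators: any parent's subscription in the Objective 1 text and the Table 2 success criterion, an LOE parent's subscription in Table 1 and the Table 2 indicator

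*Protocol article*

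**What the plan says.** All places are in the Protocol article.

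- **Feasibility objective outcomes, text.** The pass rule for Objective 1 is that it "will be met if at least 75% of enrolled families have at least one parent who subscribes to use vFCR". The subscribing parent's language is not restricted. As to its purpose, the same section says that it "will measure the reach of vFCR for LOE families".
- **Table 2, success criterion.** "Subscription of at least one parent to vFCR will be at least 75% among LOE-enrolled families". The families are restricted by language; the subscribing parent is not.
- **Table 2, indicator, same row.** "At least one LOE parent subscribes to vFCR".
- **Table 1 (Outcomes).** The primary outcome is named "LOE Parent subscription".
- **Setting and population.** A family is eligible with "at least one adult (aged 18 years or older) parent with a preferred language that is other than English".
- **Study overview.** If the health record lists more than one parent, "both parents will be separately invited to subscribe to vFCR". No language condition is attached.
- **Data collection.** For Objective 1, LOE-eligible infants are counted by chart review and the percentage subscribed is taken from that total. It is not said whose subscription counts.

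**The concern.** The trial has one primary pass/fail rule, and its numerator is printed in two forms. The forms would be equivalent if every parent in an enrolled family preferred a language other than English, but eligibility does not require that. Where one parent prefers English, that parent can be the only subscriber. The family then counts toward the 75% under the text and the success criterion, but not under Table 1 or the indicator.

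Two things are at stake. First, the primary result could be read as met or not met depending on which line is applied, and the choice could be made after the counts are known. Second, the section Objectives and trial design sets out to test feasibility among LOE parents, using language-appropriate materials and interpreters. A subscription by an English-preferring partner alone does not show that an LOE parent was reached.

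**Working it through.** **1. The definitions side by side**

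| Place | Whose subscription counts | Family where only the English-preferring parent subscribes |
|---|---|---|
| Objective 1 text | any parent | success |
| Table 2, success criterion | any parent | success |
| Table 2, indicator | LOE parent | failure |
| Table 1, outcome name | LOE parent | failure |
| Data collection, Objective 1 | not stated | undetermined |

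The conflict lies between the text and Table 1, and also inside one row of Table 2. The any-parent count can never be below the LOE-parent count, so any difference favours success.

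**2. The plan's own figure**

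Sample size gives n = 36 and error margins of at most 16.3 percentage points. The 95% Wald half-width at p = 0.5 is 1.96 × √(0.25/36) = 0.1633, so the figure is reproduced. The Wilson half-width, the method named under Statistical methods, is 0.155 at the same point and also meets the statement. Neither depends on which parent counts, because the denominator is enrolled families in both cases.

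**3. What one family is worth**

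- Threshold at n = 36: 0.75 × 36 = 27 families.
- Threshold at the anticipated maximum of 45: 0.75 × 45 = 33.75, so 34 families.
- One reclassified family: 1/36 = 2.8 points, or 1/45 = 2.2 points.

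| LOE parent subscribes | Only the English-preferring parent subscribes | LOE-parent rule | Any-parent rule |
|---|---|---|---|
| 25 | 2 | 25/36 = 69.4%, not met | 27/36 = 75.0%, met |
| 23 | 4 | 23/36 = 63.9%, not met | 27/36 = 75.0%, met |

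These counts are illustrations chosen to land on the threshold. They are not forecasts.

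**4. Chance of meeting the rule, under assumptions**

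The protocol gives none of the following, so they are assumed:

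- s: true LOE-parent subscription rate, taken as equal in mixed and other families
- m: share of mixed-language families
- q: chance that the English-preferring parent subscribes when the LOE parent does not

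The any-parent rate is s + m(1 − s)q. For s = 0.65, m = 0.2, q = 0.8 it is 0.65 + 0.2 × 0.35 × 0.8 = 0.706. The table gives the binomial probability of at least 27 of 36.

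| s | LOE-parent rule | Any-parent, m = 0.1, q = 0.5 | Any-parent, m = 0.2, q = 0.8 | Any-parent, m = 0.4, q = 0.8 |
|---|---|---|---|---|
| 0.60 | 0.045 | 0.073 | 0.181 | 0.468 |
| 0.65 | 0.138 | 0.193 | 0.354 | 0.653 |
| 0.70 | 0.325 | 0.399 | 0.577 | 0.816 |

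With m = 0 every any-parent column equals the LOE-parent column. The difference runs from nothing, through a few points when mixed families are rare, to a large gap when they are common.

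**The case against.** **A family-level reading is coherent.** The stated purpose of Objective 1 refers to LOE families, the family is the unit of inclusion, and both sentences that state the pass/fail rule accept any parent. On that view, Table 1 and the indicator are loosely worded labels. This stands as a possible reading, but it does not remove the contradiction: the indicator is what the table says is measured, and it names the LOE parent.

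**The effect has no documented size.** This stands. No section gives the share of mixed-language families. A reader might infer that reach is biased upward by a meaningful amount; the documents show only that it can be, and in which direction.

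**Other reporting softens it.** The Quantitative phase section plans to report Reach by parent and family characteristics, and the Wilson interval at 27/36 runs from 58.9% to 86.2%, wide against 2.8 points per family. Both help interpretation, but neither decides whether the 75% rule is met. That the trial does not test efficacy limits the consequences; it does not make the primary criterion unambiguous.

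**Stronger readings that the documents do not support.**

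- A reader might infer that both tables consistently require an LOE parent. Only the indicator column of Table 2 does; its criterion column agrees with the text.
- A reader might infer that Objective 2 has the same defect. Its text, indicator, criterion and Table 1 entry all leave the parent's language unrestricted, so they do not conflict. Use is tracked by application logins, which are not shown to be attributed to an individual parent.
- A reader might infer that the any-parent rule only repeats what the group has already shown. The Introduction reports better engagement in rounds among English-speaking families, not subscription by English-preferring parents in mixed-language households.

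**Conclusion.** The concern holds for Objective 1 only. The primary feasibility criterion carries two numerators that classify the same family differently whenever only an English-preferring parent subscribes, and the eligibility and invitation rules allow that to happen. The article elsewhere separates parents by language: Objective 3 is limited to encounters attended by an LOE parent, and for the survey "this parent will be the parent with a language preference other than English". The distinction is therefore one the authors already make.

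At n = 36 each such family is worth 2.8 points toward a threshold of 27 families, always in the favourable direction. How many there will be cannot be derived from the article, and if there are none the two definitions agree. The probabilities in the working rest entirely on assumed values of s, m and q. The contradiction itself rests on no assumption. It matters because it sits in the primary decision rule.

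**What to change.** Use one numerator in the Objective 1 text, both Table 2 columns and the Objective 1 sentence under Data collection: a family counts if at least one parent whose preferred language is other than English subscribes. This agrees with Table 1, the existing indicator and the aim under Objectives and trial design. Report the any-parent percentage beside it as a secondary description. Settle this before subscription counts are examined.

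Objective 2 needs no correction on this ground. Use by LOE parents could be described where logins or observation of rounds identify the parent.

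**Cost.** The change is mainly wording. Parents subscribe individually with their own contact details, and parent-level language is already needed for Objective 3 and the surveys. The research log has to show which parent subscribed and that parent's preferred language. The sample size, the denominator and the 27-of-36 threshold stay as they are. The primary percentage may come out slightly less favourable.
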